#### Proposed Method: Interpretable SERT

SERT consists of 3 scoring algorithms, each tailored to its application at different time points in the ED. On arrival at the triage station, SERT-1 is used to estimate patients’ likelihood of admission (inpatient and ICU) and 2-day mortality. SERT-1 is intended to assess the patient’s immediate urgency based on basic patient information, simple vital measurements, and medical histories readily available during triage. While in the ED, SERT-2 predicts patients’ admission (inpatient and ICU) and 2/7-day mortality using a variety of variables, including laboratory test results, vital signs, ED treatment, diagnosis, and some administrative information. As an extension of the SERT-1 algorithm, SERT-2 incorporates additional variables obtained during ED stay to better predict outcomes. On admission, SERT-3 predicts the likelihood of 7/30-day mortality, ICU transfer, and prolonged length of stay using variables collected in the ED and during the first 24 hours of inpatient stay. In actual clinical implementation, in the case where a patient has incomplete information, SERT will use imputation methods to fill in the missing values before calculating the risk score. In summary, SERT allows for a comprehensive risk assessment and prediction in the ED in a dynamic manner.

The clinical risk-scoring models have been traditionally developed in 2 ways: through expert opinions or consensus and conventional cohort studies. However, both approaches are labor-intensive and are not easy to update over time. Recently, we developed an interpretable machine learning–based automatic clinical score generator, AutoScore, as a practical and universal solution for risk scoring [29]. Using the AutoScore framework, users could seamlessly generate parsimonious risk models (ie, point-based sparse risk scores), thereby supporting automated machine learning solutions in health care [43]. AutoScore comprises 6 modules. In module 1, random forest is used to rank variables in terms of their contribution to modelling. Module 2 categorizes continuous variables to address nonlinearity and facilitate the generation of point-based scores. Module 3 computes scores based on a subset of variables and logistic regression, while module 4 determines the optimal number of variables based on a parsimony plot. Module 5 enables fine-tuning of the cut-off values for categorizing continuous variables for preferable interpretation, and module 6 provides a final performance evaluation. AutoScore is used to develop the 3 SERT scoring algorithms with the candidate variables and the outcomes.

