**Methods:**

To achieve this objective, we will conduct a retrospective, single-center study based on a large, longitudinal data set obtained from the EHRs of the largest tertiary hospital in Singapore. Study outcomes include adverse events experienced by patients, such as the need for an intensive care unit and inpatient death. With preidentified candidate variables drawn from expert opinions and relevant literature, we will apply an interpretable machine learning–based AutoScore to develop 3 SERT scores. These 3 scores can be used at different times in the ED, that is, on arrival, during ED stay, and at admission. Furthermore, we will compare our novel SERT scores with established clinical scores and previously described black box machine learning models as baselines. Receiver operating characteristic analysis will be conducted on the testing cohorts for performance evaluation.

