### Outcomes

The clinical outcomes in this study include the following adverse events experienced by patients during their inpatient stay:

Admission: A hospital admission following an ED visit [37-39]. Each ED attendance is classified as admission or discharge according to the clinical decision made. As a result, patients who left before a decision could be made are excluded rather than considered discharged.Inpatient death: A clinically certified death of a patient admitted to the hospital and who died during the hospitalization.2/7/30-day mortality: A clinically certified death of an admitted patient that occurred 2/7/30 days after the ED visit regardless of the place of death.ICU transfer: Identified using the hospital’s admission, transfer, and discharge database. Whenever a patient had more than one transfer from ward to ICU, only the data before the first transfer were included.Cardiac arrest: Defined as the loss of a palpable pulse with attempted resuscitation in the ward.Prolonged hospital length of stay: Defined as 21 days or more for the hospital stay.

**Table 1 table1:** List of the high-level constructed variables in the master data set, along with their sources and categories.

Category	Subcategory	Source table	High-level variables extracted

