**Information collected within the first 24 hours of inpatient stay**			
	Inpatient stay patient flow	Inpatient movement	ICU or HDU admission, ward class, duration of ICU or HDU stay, hospital departments, surgeries
	Inpatient vital	Inpatient vital signs	Pulse, respiration, SpO_2_, systolic BP, diastolic BP, temperature, Glasgow coma scale, height, weight, BMI
	Inpatient laboratory	Inpatient laboratory	Laboratory measurement frequency and major laboratory test results: albumin, potassium, creatinine, sodium, bicarbonate, creatine kinase, creatine kinase_MB (mass), C-reactive protein, prothrombin time, procalcitonin, blood PH, glycated hemoglobin A1c, triglycerides, cholesterol, high-density lipoprotein cholesterol, low-density lipoprotein cholesterol
	Inpatient treatment	Inpatient treatment and order	Major medication prescription and order

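### SERT-3 is to be used at admission but needs the first 24 inpatient hours of data, and its outcomes are counted from before that window closes

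*Protocol article*

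**What the plan says.** **Time of use.** The section Proposed Method: Interpretable SERT describes three algorithms, "each tailored to its application at different time points in the ED". For the third it says: "On admission, SERT-3 predicts the likelihood of 7/30-day mortality, ICU transfer, and prolonged length of stay". The Abstract (Methods) gives the same timing: "These 3 scores can be used at different times in the ED, that is, on arrival, during ED stay, and at admission".

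**Predictors.** The sentence that places SERT-3 at admission ends: "ICU transfer, and prolonged length of stay using variables collected in the ED and during the first 24 hours of inpatient stay". Table 1, in the block for the first 24 inpatient hours, lists under patient flow "ICU or HDU admission, ward class, duration of ICU or HDU stay, hospital departments, surgeries". The source table is Inpatient movement, which is also one of the two source tables for the ICU-transfer outcome.

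**Outcomes.** The Outcomes section takes ICU transfer from the admission, transfer and discharge database and gives it no start time. Mortality at 7 and 30 days is timed from the ED visit. The only rule that cuts predictor data at an event is: "Whenever a patient had more than one transfer from ward to ICU, only the data before the first transfer were included".

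**The concern.** A prediction model needs one moment at which the score is issued, with predictors before it and outcomes after it. SERT-3 has no such moment. It is assigned to admission, its predictors run to 24 hours later, and its outcomes start at or before admission.

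Two things follow. First, the performance reported for SERT-3 would describe a score that nobody can calculate at admission. Second, part of the validation would concern events that fall inside the predictor window. A ward-to-ICU move at hour 10 counts as an ICU-transfer outcome, and it may also set the first-24-hour ICU variable. A patient who dies at hour 10 counts as a 7-day death and is scored on data running up to that death.

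The planned validation would not reveal this. The 2019 and 2020 testing cohorts use the same variable and outcome definitions as the development data, so the overlap recurs in both. SERT-3 is one of the study's three deliverables, and its AUC is to be compared with that of established clinical scores and black box models.

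**Working it through.** The article gives no AUC, event rate or timing distribution for SERT-3, so there is no figure to reproduce. The check is a timeline, followed by an illustration under stated assumptions.

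**Timeline, with admission at t = 0**

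| Element | Position | Source |
|---|---|---|
| Time of use | t = 0 | Abstract; Proposed Method |
| Predictor window closes | t = 24 h | Proposed Method; Table 1 |
| ICU transfer counted from | no start time after 24 h | Outcomes |
| 7/30-day mortality counted from | ED visit, before t = 0 | Outcomes |

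The predictors run 24 hours past the time of use. They share up to 24 hours with the period in which outcomes are counted.

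**Illustration for ICU transfer.** None of these inputs is in the document:

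- A0 = 0.80, the AUC without leakage (binormal).
- f, the share of transfers within 24 hours that set the ICU flag: 20%, 30% or 50%.
- g, the share of non-events also flagged, for example by HDU admission or direct ICU admission from the ED: 0%, 5% or 10%.

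With g = 0, every flagged case outranks every non-case, so

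apparent AUC = f + (1 − f) × A0.

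- f = 0.2: 0.2 + 0.8 × 0.80 = 0.84
- f = 0.3: 0.3 + 0.7 × 0.80 = 0.86
- f = 0.5: 0.5 + 0.5 × 0.80 = 0.90

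With g > 0 and the best combination of score and flag, let μ = √2 × Φ⁻¹(0.80) = 1.190 and d = ln[f(1 − g) / (g(1 − f))]. Then

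AUC = [fg + (1 − f)(1 − g)] × 0.80 + f(1 − g) × Φ((μ² + d)/(√2 μ)) + (1 − f)g × Φ((μ² − d)/(√2 μ)).

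For f = 0.2 and g = 0.05, d = ln 4.75 = 1.558 and the two Φ terms are 0.961 and 0.467. The AUC is 0.77 × 0.80 + 0.19 × 0.961 + 0.04 × 0.467 = 0.817.

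| f | g = 0 (maximum) | g = 5% | g = 10% |
|---|---|---|---|
| 20% | 0.84 | 0.82 | 0.81 |
| 30% | 0.86 | 0.84 | 0.82 |
| 50% | 0.90 | 0.88 | 0.86 |

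In simulation, restricting to patients not yet transferred at 24 hours brings the AUC back to 0.80. No comparable calculation is offered for death, because ICU admission is not the death outcome.

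**The case against.** The strongest reply accepts that the timing wording conflicts but denies that leakage is shown.

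- **Table 1 describes the master data set.** It mixes predictors with outcomes and does not say that every first-24-hour row enters SERT-3. The Variable Construction section also says irrelevant or repeated variables will be dropped. This stands in part: a reader might infer that ICU admission is a fixed SERT-3 predictor, and the text does not say so. It does offer first-24-hour variables to SERT-3 without excluding the ICU items, so leakage is possible but not established.
- **The pre-transfer rule may be meant for everyone.** It can be read as choosing the index transfer when there are several, on the understanding that only pre-transfer data are used for any transferred patient. That reading is fair, so it cannot be asserted that single-transfer patients contribute later data. But the wording covers only patients with more than one transfer. Even on the broad reading it does not address early deaths, and it leaves the time of use unreconciled.
- **Death does not leak.** Correct. ICU admission is a legitimate prognostic variable for later death. What remains is that patients who die within 24 hours are scored on data up to the event.
- **Variable ranking.** A reader might expect AutoScore to rank the ICU variables first. Nothing in the description of its modules supports that prediction.
- **Imputation could fill the gap at admission.** The article does plan to impute incomplete information when the score is used. At admission, however, every first-24-hour variable would be missing for every patient, so the tested performance would not carry over.
- **A condensed article leaves such details elsewhere.** Risk sets and final predictor lists may be left out. Here the article itself fixes a time of use and a predictor window that contradict each other, and that is not an omission.

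**Conclusion.** The point holds for timing without further assumptions: as written, SERT-3 cannot be computed at its stated time of use, and its predictor and outcome windows overlap by up to 24 hours. Direct entry of the outcome into the predictors is a risk for ICU transfer only, and it depends on whether the ICU items are offered to the model and how the pre-transfer rule is applied. For 7/30-day death the fault is window overlap.

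The document does not allow the bias to be sized. The figures 0.84, 0.86 and 0.90 might be taken as the expected inflated AUC. They are upper limits for the assumed f and A0, because they allow no flagged non-events; with 5-10% flagged, the gain over 0.80 is about 0.01 to 0.08. The point should be settled before modelling, since one of the three scores cannot otherwise be interpreted.

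**What to change.** Reconcile the time of use with the predictor window in one of two ways.

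(a) **Issue SERT-3 at 24 hours after admission.** Develop and test it only in patients who are alive, still in hospital and, for ICU transfer, not yet in ICU at 24 hours. Count outcomes only after that point. ICU admission and ICU duration then drop out as predictors of ICU transfer; HDU variables may stay, since they precede the outcome in this cohort.

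(b) **Keep SERT-3 at admission.** Remove all first-24-hour inpatient variables from its candidates.

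In either case, reword the rule in Outcomes so that only pre-transfer data are used for every transferred patient, whatever the number of transfers. Align the Abstract, the SERT description and Table 1 with the choice.

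**Cost.** Only cohort, variable and outcome definitions change; the Results section says the data are still being linked and cleaned. Under (a) the cohort is somewhat smaller and SERT-3 is no longer a score used in the ED. Under (b) its predictors come close to those of SERT-2. In both, the AUC will probably be lower, but it will be valid for the stated use.

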#### Baseline Methods: Traditional Clinical Scores

Several traditional clinical scores will be calculated for performance comparison with the SERT scores. They are the PACS triage system [32], Modified Early Warning Score [44], National Early Warning Score [45], Rapid Acute Physiology Score [46], Rapid Emergency Medicine Score [47], and Cardiac Arrest Risk Triage [48].

#### Baseline Methods: Black Box Machine Learning Models

Additionally, several machine learning techniques will be compared as baselines for predictive modelling. Of the many machine learning algorithms, we will apply the following popular ones as examples.

Random forest [49]: As the most commonly used tree-based prediction tool, its R package “RandomForest” will be used for model fitting. The parameters will be selected based on recommendations made in previous literature [50,51], where *ntree*= 100 and *mtry* is the principal square root of *m* (*ntree* number of trees grown; *mtry*: number of variables randomly sampled as candidates at each split).Least absolute shrinkage and selection operator [52]: As a penalized regression technique, it is another popular method used in clinical modelling. It is a regression-based method that employs a regularization process for variable selection to increase the statistical model’s predictive accuracy and interpretability. In our study, its regularization rate will be optimized through 10-fold cross-validation.Deep learning [53]: As a branch of the machine learning field that uses deep neural networks, deep learning was initially widely adopted for computer vision and image understanding before being used for medical image analysis. More recently, researchers have begun to explore deep learning for EHR analysis [54,55]. We are particularly interested in applying deep learning algorithms for adverse event prediction, drawing on the rich sources of EHR data, as described earlier. Using the PyTorch library, we will construct a long short-term memory network [56]. In addition, a multilayer perceptron [57] will be used in conjunction with long short-term memory to learn nontemporal data.

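### The random forest baseline is fixed at 100 untuned trees, which may understate its AUC for rare outcomes and so favour SERT in that one comparison

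*Protocol article*

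**What the plan says.** In the protocol article, under Baseline Methods: Black Box Machine Learning Models, the forest is fitted in R ("its R package “RandomForest” will be used for model fitting"), and its settings come from earlier publications: "The parameters will be selected based on recommendations made in previous literature [50,51], where *ntree*= 100 and *mtry* is the principal square root" of the number of variables. Terminal node size and the form of the output (vote share or averaged probability) are not given.

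The same section treats the LASSO differently: "its regularization rate will be optimized through 10-fold cross-validation". A third baseline, a long short-term memory network combined with a multilayer perceptron, has neither fixed settings nor described tuning.

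Under Proposed Method: Interpretable SERT, "module 4 determines the optimal number of variables based on a parsimony plot", and "Module 5 enables fine-tuning of the cut-off values for categorizing continuous variables for preferable interpretation". The section Predictive Modelling for Clinical Decision Making sets aside 20% of the 2008–2018 visits as a validation cohort. Under Model Comparison and Performance Metrics, the overall measure is the area under the ROC curve on two testing cohorts, with sensitivity and specificity read at the point nearest the upper-left corner.

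**The concern.** Comparing SERT with black box algorithms is a stated objective. The forest is the only model in that comparison whose settings are fixed outright; SERT and the LASSO each have a selection step based on the study's own data.

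A forest of 100 hard-voting trees can give only 101 distinct scores, in steps of 1%. For an outcome rarer than that step, many patients may receive no votes. The AUC counts each tied event/non-event pair as one half, and no threshold can separate patients within the tied block. The forest could then look weaker than the method is, and the error would favour SERT on the rarest and gravest outcomes.

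**Working it through.** **Inputs.** From the article: 100 trees; mtry = √m; AUC as the metric; more than 1.8 million visits; about 650,000 admissions. Assumed: event rates other than admission, fully grown trees, hard votes. Tree count is a design choice, so there is no derived figure to reproduce.

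**Step 1: the one event rate that can be derived.** Admission: 650,000 / 1,800,000 = 36%.

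**Step 2: exact tie probability.** If each tree votes for the event with probability q, then P(no votes from 100 trees) = (1 − q)^100.

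| q | P(no votes) |
|---|---|
| 0.1% | 90% |
| 0.5% | 61% |
| 1% | 37% |
| 2% | 13% |
| 4% | 2% |
| 36% | 0% |

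**Step 3: patients who differ in risk.** Let q be logit-normal, calibrated to the event rate and to a large-forest AUC of 0.80 or 0.90, with votes Binomial(100, q) and a tie-corrected AUC. Each cell gives the result for 0.80, then for 0.90.

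| Event rate | Tied at zero | AUC with 100 trees |
|---|---|---|
| 0.1% | 92%, 93% | 0.59, 0.71 |
| 0.5% | 70%, 79% | 0.69, 0.82 |
| 1% | 55%, 69% | 0.73, 0.85 |
| 2% | 38%, 57% | 0.76, 0.87 |
| 4% | 23%, 44% | 0.78, 0.88 |
| 36% | 0.6%, 7% | 0.80, 0.90 |

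So more than half of patients tie at rates up to about 1%, or about 2% if discrimination is strong. At a 0.5% rate with large-forest AUC 0.80, 38% of the events themselves sit at zero votes. Any threshold above zero then has sensitivity of at most 62%. In that case more hard votes recover AUC slowly: 0.690 with 100 trees, 0.764 with 500, 0.780 with 1000, 0.789 with 2000.

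**Step 4: fitted forests on simulated data.** There were 25 predictors and mtry = 5, with 80,000 training visits at 0.3% and 40,000 at the other rates. The last forest column changes two things together: terminal nodes of at least 200, and averaged probabilities in place of votes.

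| Event rate | Tied at zero, 100 trees | AUC, 100 trees | AUC, 500 trees | AUC, 100 trees, larger nodes and probabilities | AUC, 6-variable point score |
|---|---|---|---|---|---|
| 0.3% | 82% | 0.747 | 0.820 | 0.859 | 0.870 |
| 1% | 58% | 0.786 | 0.823 | 0.872 | 0.858 |
| 3% | 29% | 0.824 | 0.841 | 0.860 | 0.834 |
| 36% | 0% | 0.808 | 0.813 | 0.799 | 0.767 |

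A separate simulation with 40,000 training visits points the same way. Going from 100 to 400 fully grown trees raised AUC from 0.679 to 0.727 at 0.3% events and from 0.736 to 0.772 at 1%.

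At 1% and 3% the point score beats the 100-tree forest but loses to the forest with larger nodes and averaged probabilities. The forest settings can therefore reverse the ranking.

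**The case against.** The strongest objection is that the tie problem depends on settings the article does not state. Node size and output type are absent, an article may leave them to a fuller plan, and the cited recommendations cannot be checked here. This stands, and it makes the size of the effect conditional. It does not remove the point, because tree count and mtry are stated and fixed.

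Other objections also stand in part:

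- **Tree count is not the sole cause.** In the simulations, larger nodes with averaged probabilities gained more at the low rates than going to 500 trees did.
- **Event rates are assumed.** The Outcomes section defines 2-, 7- and 30-day mortality as deaths of admitted patients. If admissions rather than all visits are the denominator, rates are about 1,800,000 / 650,000 = 2.8 times higher and ties are fewer. SERT-3, used on admission, has that denominator.
- **The simulated AUCs do not transfer.** If visits are spread evenly over the 13 years, the real training cohort is about 1.8 million × 11/13 × 0.8 = 1.2 million visits. The simulated predictors were artificial, and the point score was given the six strongest variables.
- **The tuning contrast is softer than it looks.** The cut-off step in SERT serves interpretation, and the parsimony plot trades performance for fewer variables.

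A reader might infer that the black box comparison as a whole is tilted towards SERT, or that the study claims parity with black box models. The documents support neither. The forest is one of three machine learning baselines, the LASSO is tuned, and the article promises only a comparison.

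**Conclusion.** The point holds in a limited form. The forest is committed to 100 trees and a default mtry without tuning, while SERT and the LASSO are fitted with selection steps. For outcomes at an assumed rate of about 1% or less, and with fully grown trees and vote-share output, a large share of patients would tie at zero. This lowers the AUC of this one comparator and favours SERT against it. Two-day mortality over all ED visits is the plausible case.

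The effect is modest at about 3% (0.017 AUC between 100 and 500 trees in simulation) and negligible for admission (0.005). A reader might go further and say that most patients will tie, or that the loss will be the simulated 0.04 to 0.07 between 100 and 500 trees at the lower rates. The article gives no mortality rate, node size or output type from which to establish that. The simulations show direction only.

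**What to change.** Replace the fixed settings with a short tuning rule for the forest, applied separately to each outcome:

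- Choose terminal node size and mtry by cross-validation in the training cohort or on the existing 20% validation cohort. Node size should not be set once for all outcomes: in the simulation, nodes of at least 200 helped at low rates but gave 0.799 against 0.808 at 36%.
- Raise the number of trees until AUC is stable, for example starting from 500. With hard votes and very rare events, 500 may not be enough.
- Use averaged probabilities in place of hard votes, and state the output type.

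No new data are needed and the testing cohorts stay untouched. The cost is computing time on a training set of over a million visits, and possibly a different implementation if the named package does not give averaged probabilities. If the 100-tree forest is kept, the report should state the share of patients at zero votes for each outcome. It should also say that a SERT advantage over this forest on rare outcomes is not evidence about black box models in general.
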